#### Control

Participants in the WLC group will receive no treatment and will continue with their usual parenting practices in managing their children. After a 1-month follow-up, the participants will be given access to the DaPI program.

#### Outcome measures

Parents in both the DaPI and WLC groups will complete a questionnaire comprising the following questions at pre- (baseline) and post-intervention (8 weeks) and at the 1-month follow-up mark. Parents in the DaPI group will be allowed to complete the questionnaire, regardless of whether they have completed all eight sessions of the DaPI program. Prior to answering the questionnaire, parents with more than one child within the required age range will need to select a child as the focus of the study. If both parents in the same household wished to participate, they would choose a different focus child within the stipulated age range. The questionnaire will be administered in Malay. A forward backward translation procedure will be conducted for questions that have not been translated and validated in a Malaysian sample.

#### Primary outcomes

##### Parenting measures

(a). Parenting behavior—Parenting behavior of parents will be measured using a self-report multidimensional assessment of parenting scale (MAPS; Parent and Forehand, 2017). This 34-item scale comprises two broad domains (i.e., Positive and Negative Parenting) and seven narrowband domains of parenting practices. Out of the seven narrowband domains, four (i.e., Proactive Parenting, Positive Reinforcements, Warmth and Supportiveness) are in the positive parenting domain, while three (i.e., hostility, physical control, and lax control) in the negative parenting domain. Items are rated on a 5-point Likert scale ranging from 1 (never) to 5 (always). Total scores are obtained by summing up all items in the respective domains, where higher scores on the positive parenting domain indicate higher levels of warmth, supportiveness, and good positive control. Contrarily, higher scores on the negative parenting domain reflect higher levels of hostility as well as both over- and under-control. The internal consistency for both the positive and negative parenting dimensions are reported to be strong, with α = 0.90 and 0.88, respectively (Parent and Forehand, 2017). Similarly, all seven (7) narrowband domains reported good to excellent reliability ranging from 0.77 to 0.91 (Parent and Forehand, 2017).

(b). Parental self-efficacy–Parental self-efficacy will be measured using the 20-item subscale of the Child Adjustment and Parent Efficacy Scale (CAPES; Morawska et al., 2014). Parents will rate their self-efficacy in managing their child’s behavioral and emotional health over the last 4 weeks using a 4-point scale ranging from 0 (not true of my child at all) to 3 (true of my child very much, or most of the time). The total scores will be obtained by the summation of all items, where higher scores indicate better self-efficacy in dealing with children’s mental health. This subscale has been reported to have good internal consistency, with a Cronbach’s alpha of 0.96 (Baker, 2016).

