#### Secondary outcome

##### Children mental health measure

Parents’ perceptions of their children’s mental health will be based on the 30-item Child Adjustment and Parent Efficacy Scale (CAPES; Morawska et al., 2014). This scale comprises two subscales that assess children’s behavioral problems and emotional maladjustment. Parents will rate their child’s behavioral problems and emotional maladjustment over the last 4 weeks on a scale ranging from 0 to 3 (0 = not true of my child at all; 3 = true of my child very much, or most of the time). The total score will be calculated by summing all 30-items (score range 0–90), where higher scores indicate a higher intensity of problems. The CAPES has been found to have good internal consistency (α = 0.90). Similarly, the behavioral subscale (α = 0.90) and emotional maladjustment (α = 0.74) were found to have a high level of reliability (Morawska et al., 2014).

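### The primary outcome parental self-efficacy is given response anchors about the child, identical to those of the child-problem scale, which do not express a parent's self-efficacy

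*Protocol article*

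**What the plan says.** Under Primary outcomes, Parenting measures, item (b), the article states: "Parental self-efficacy will be measured using the 20-item subscale of the Child Adjustment and Parent Efficacy Scale". With a 4-week recall, parents are to rate their self-efficacy in managing the child's behavioural and emotional health. The response format is given as "using a 4-point scale ranging from 0 (not true of my child at all) to 3 (true of my child very much". Scoring is a plain sum: "The total scores will be obtained by the summation of all items, where higher scores indicate better self-efficacy in dealing with" the child's mental health. No score range is given.

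Under Secondary outcome, Children mental health measure, the article describes a 30-item scale under the same instrument name: "This scale comprises two subscales that assess children’s behavioral problems and emotional maladjustment". The recall period is again 4 weeks and the anchors are "0 = not true of my child at all; 3 = true of my child very much, or most of the time". The score is obtained by "summing all 30-items (score range 0–90), where higher scores indicate a higher intensity of problems".

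The Objective section predicts higher self-efficacy in the intervention group. The Statistical analyses section calls the intervention effective if the intervention group improves more than control on one of the outcome variables at the 0.05 level, with a small to medium effect size.

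**The concern.** A response scale has to fit the thing being rated. Here the parent is asked about their own self-efficacy, but the options describe the child. A parent cannot use them to say how well they feel able to manage a behaviour.

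The options printed for self-efficacy are those printed for child problems, with the same 0 to 3 coding and the same recall period. The likeliest explanation is that text was carried over from one paragraph to the other, but nothing in the article shows that the form itself is different.

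Two things are at stake. First, a primary outcome might not measure what it is named for. The study's reasoning is that better parenting and higher self-efficacy lead to better child mental health, and that cannot be examined if the self-efficacy rating is partly a rating of the child. Second, the success rule is met by improvement on a single outcome variable, so an outcome with an unclear meaning could alone decide the trial's conclusion.

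**Working it through.** The question is one of definition, so the main check is to set the two sections side by side.

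| | Self-efficacy (primary) | Child mental health (secondary) |
|---|---|---|
| Instrument named | Child Adjustment and Parent Efficacy Scale | same |
| Items | 20 | 30 |
| Who is rated | the parent | the child |
| Anchors, 0 to 3 | truth of something about the child | identical |
| Recall | last 4 weeks | last 4 weeks |
| Scoring | plain sum | plain sum |
| Higher means | better self-efficacy | more problems |
| Range stated | none | 0–90 |

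**Range.** Maximum score = items × highest item code. For the child scale, 30 × 3 = 90, which reproduces the stated 0–90. The same rule gives 20 × 3 = 60 for self-efficacy as written, so 0–60.

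**Do the anchors fit the construct?** For the child scale they do. Most of the other scales whose end points are printed also fit: never to always for parenting behaviour, disagreement to agreement for self-esteem, and how far a symptom applied to the respondent for parental mental health. The self-efficacy anchors are the exception, because they do not describe the respondent's efficacy.

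**Is a correct format given elsewhere?** No. Self-efficacy has no other response format in the article. The secondary section lists only two child subscales within the 30 items, so it does not show where the 20-item efficacy subscale sits or how it is answered.

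**What would a high score mean?** Take a parent who answers 3 on every item and scores 60. There are two readings:
- If the 20 items are statements about child problems, 60 is the maximum of problems and would be read as the maximum of self-efficacy. The sign would be reversed.
- If the 20 items are about the parent's confidence, the anchor does not answer the question put, and 60 has no defined meaning.

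The article does not print the items, so it cannot decide between these. In neither case do the printed anchors yield a valid self-efficacy score.

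**Is reverse scoring implied?** It is stated for the self-esteem scale, where negatively worded items are reversed before summing. None is stated here, so it cannot be assumed.

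**Effect on the design figures.** None. The minimum of 128 reproduces (two-sided two-sample t-test, standardised effect 0.50, alpha 0.05, power 0.80: 63.77, rounded up to 64 per group, and 2 × 64 = 128). It does not depend on how self-efficacy is rated.

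**The case against.** The strongest reply is that this is a slip in a condensed article. The instrument is named and cited, and the construct, item count and direction are all given. The form actually fielded may carry the right options, and the article does not say that the form is built from this paragraph. That stands as a limit: the harm is conditional on the text being followed. It does not remove the point, because this is not detail left to a fuller document. A specific response scale is printed for a primary outcome, and it does not fit. The planned forward and backward translation would not correct it either, since translation reproduces the source wording.

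A reader might also infer that the two scoring directions contradict each other, because the same anchors mean better in "where higher scores indicate better self-efficacy" and worse in "where higher scores indicate a higher intensity of problems". The documents do not support that. Different item sets can share response options and run in opposite directions. The parenting behaviour scale in the same section does so, with one never-to-always scale for its positive and negative domains.

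Nor do the documents support a numerical size for a sign reversal. That would need the item wording and the overlap between the 20-item and 30-item scores, and neither is shown. It would likewise go too far to say that the quoted internal consistency of 0.96 is lost, because the response format behind that figure is not visible.

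**Conclusion.** The point holds as an internal inconsistency in the definition of a primary outcome. The anchors printed for parental self-efficacy are those of the child-problem scale and do not express the parent's self-efficacy.

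The consequence is conditional. If the form is built as written, one of the two primary outcomes would not validly measure its stated construct, and what a higher score means would be unclear. A reversed sign remains only a possibility, dependent on the 20 items being statements about child problems. No bias can be quantified from the documents, and no sample size, power or alpha figure is affected.

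It still needs correcting before the outcome is used, because the outcome is primary and the success rule can be met on one outcome variable alone.

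**What to change.** Reconcile item (b) of Parenting measures and the Children mental health measure section with the cited instrument. In item (b), replace the anchors with that instrument's own self-efficacy response format, and state the resulting score range and direction. Say also how the 20-item efficacy subscale relates to the 30 child items.

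Then check the Malay online form against the corrected text before enrolment. If the form is already in use, confirm before analysis which anchors parents were shown, and record this.

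The cost is a text correction and one check of the form. No extra assessments or participants are needed.

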#### Secondary outcome

##### Children mental health measure

Parents’ perceptions of their children’s mental health will be based on the 30-item Child Adjustment and Parent Efficacy Scale (CAPES; Morawska et al., 2014). This scale comprises two subscales that assess children’s behavioral problems and emotional maladjustment. Parents will rate their child’s behavioral problems and emotional maladjustment over the last 4 weeks on a scale ranging from 0 to 3 (0 = not true of my child at all; 3 = true of my child very much, or most of the time). The total score will be calculated by summing all 30-items (score range 0–90), where higher scores indicate a higher intensity of problems. The CAPES has been found to have good internal consistency (α = 0.90). Similarly, the behavioral subscale (α = 0.90) and emotional maladjustment (α = 0.74) were found to have a high level of reliability (Morawska et al., 2014).

#### Other measures

##### Personal characteristics

Information on parents’ personal characteristics, such as age, education, occupation, marital status, race, self-esteem, and mental health (i.e., depression, anxiety, and stress) will be monitored.

(a) Self-esteem: Parents’ self-esteem will be measured using the Rosenberg Self-esteem Scale (Rosenberg, 1965). This scale comprises 10 items and rated on a 4-point Likert scale ranging from “strongly disagree” to “strongly agree.” Total scores will be obtained by summing all items after reverse-scoring negatively worded items. Higher scores indicate higher self-esteem. The internal consistency of this scale has been reported to be excellent (α = 0.92; Rosenberg, 1965).

(b) Mental health: Parents’ symptoms of depression, anxiety, and stress will be assessed using the Malay version of the Depression Anxiety Stress Scales-21 (DASS-21; Musa et al., 2007). Parents will rate the extent to which items were applied to them over the past week on a 4-point scale ranging from “did not apply to me at all’ to “applied to me very much, or most of the time.” Higher scores will suggest poorer mental health. The internal consistency for the overall scale was reported to be very good, with a Cronbach’s alpha of 0.90. Similarly, all subscales had good internal consistency (α ^Depression^ = 0.84, α ^Anxiety^ = 0.74, α ^Stress^ = 0.79) (Musa et al., 2007).

##### Child characteristics

Information on the focus child’s personal characteristics, such as age, sex, and education will be focused on.

##### Family social context

Information on family characteristics such as family income, number of children, family structure (intact/non-intact), and family relations (i.e., parent-child conflict and family cohesiveness) will also be dealt with.

(a) Parent-child conflict—Parents’ perception of the intensity of their parent–child conflict will be assessed using the 6-item short version of the Network of Relationships Inventory (Furman and Buhrmester, 1985; De Goede et al., 2009). Parents will indicate their answers on a five-point Likert scale (ranging from 1 = a little or not at all to 5 = more is not possible), with higher scores indicating higher levels of intensity of the parent-child conflict. Cronbach’s alpha for this scale has been reported to be high ranging from 0.90 to 0.92 (Furman and Buhrmester, 1985; De Goede et al., 2009).

(b) Family cohesion: Parents will rate family cohesion using a 9-item scale developed by Tolan et al. (1997). This scale measures how well family members communicate with each other, are emotionally close, dependent, and are supportive of one another. The parents will rate the items using a 4-point Likert scale ranging from “not true at all” to “very true.” The summation of the items indicates a higher family cohesion. Cronbach’s alpha (0.84) for this scale indicated strong reliability (Leidy et al., 2010).

##### Program use and client satisfaction measure

(a) Parent patterns of use of the DaPI program will be monitored throughout the 8-week program. At the post-intervention assessment, parents in the DaPI group will be asked to rate details about the program and comment on its content as well as features. Items are rated on a 5-point scale with responses ranging from 1 = very poor/not at all helpful/strongly disagree to 5 = very good/very helpful/strongly agree. High scores will indicate the effectiveness of the DaPI program in delivering content.

(b) Parents’ satisfaction with the DaPI program will be assessed using the eight-item Client Satisfaction Questionnaire (CSQ; Sanders et al., 2012). This scale will assess how well the program met parents’ needs, decreased dysfunctional parenting, and mental health issues of the child. Higher scores indicate higher satisfaction with the quality of service. This scale has been reported to have excellent internal consistency with a Cronbach’s alpha of 0.93 (Baker, 2016).

### Statistical analyses

Multivariate analysis of covariance (MANCOVA) will be employed to compare the mean of the outcome variables at pre-assessment, post-assessment, and 1-month follow-up between the two groups (i.e., DaPI vs. WLC). Pairwise comparisons will be performed to identify specific differences in the outcome variables between the groups. Similarly, intention-to-treat analysis (ITT) will be conducted on the data to allow all participants to be included in the analysis, regardless of whether they withdrew from the study or did not complete the intervention. Missing data will be treated using multiple imputations, which is a relatively flexible, general approach for dealing with missing data. The intervention will be considered effective if the parents in the DaPI group show more improvement over time on one of the outcome variables compared to the control group, at a significance level of 0.05, and at small to medium effect size *d* [0.2–0.5].

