**Methods:**

A total of 200 parents of children aged 10–14 years will be recruited and randomized into two groups either intervention or waitlist-control based on a 1:1 ratio for a duration of 8 weeks. Those in the intervention group will receive eight sessions of the DaPI program that focus mainly on parenting and children’s mental health. The primary outcome of this study will essentially focus on the changes in parent-reported parenting behavior and parental self-efficacy. The secondary outcome will be changes in children’s mental health (i.e., behavioral problems and emotional maladjustment). Assessments will be arranged pre- and post-intervention as well as at the 1-month follow-up. Analyses will be conducted using a paired *t*-test and multivariate analysis of covariance.

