### Participants

#### Randomization

Participation randomization to either the DaPI or WLC group will be overseen by a research coordinator. Using a simple random technique, each participant will be assigned a unique identification number generated by a random number generator in a 1:1 proportion. Immediately after the participants completed the pre-intervention questionnaire, the research coordinator will notify them of their allocation *via* email.

Participants in the DaPI group will get immediate access to the online program, by logging in with their user ID and password provided by the researcher. They will be able to access the program as per their convenience particularly, their chosen time and day. Meanwhile, participants in the WLC group will be given access to the program after the 1-month follow-up questionnaire has been collected. Figure 1 summarizes the flow of participants in this study. Due to the nature of the intervention, participants and researchers directly involved in the online intervention cannot be blinded to the allocation. Nonetheless, researchers involved in data collection and the analyses will be blinded, as they are not involved in participant allocation or online intervention.

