#### Sample size and power analysis

A power analysis using the G*Power software (Faul et al., 2007) will be performed in estimating the required sample size. To detect a medium effect size of 0.50, with alpha set at 0.05, and power of 0.80, a minimum sample size of 128 is required. Based on recommendations from Hall and Bierman (2015) review of high attrition from technology-assisted parenting intervention, this study will allow an attrition of 50%, making the target sample size 200, with 100 participants for each group.

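### The analysis section lists the baseline score among the means compared between arms and names no baseline-adjusted or change contrast, although success means greater improvement; the abstract adds a within-arm paired t-test

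*Protocol article*

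**What the plan says.** The Statistical analyses section states that MANCOVA will "compare the mean of the outcome variables at pre-assessment, post-assessment, and 1-month follow-up between the two groups", followed by pairwise comparisons between the groups. It names no covariate, change score or group-by-time term. The same section calls the intervention effective "if the parents in the DaPI group show more improvement over time" than the control group on one of the outcome variables, at the 0.05 level.

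The Randomization section fixes when the first of the three scores is taken: "Immediately after the participants completed the pre-intervention questionnaire, the research coordinator will notify them of their allocation".

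The Methods paragraph of the Abstract describes the analysis differently. It says "Analyses will be conducted using a paired" t-test together with MANCOVA. The Statistical analyses section does not mention a paired t-test.

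The Sample size and power analysis section gives the planning figures: "To detect a medium effect size of 0.50", "with alpha set at 0.05, and power of 0.80, a minimum sample size of 128 is required".

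**The concern.** Because parents complete the baseline questionnaire before they are told their arm, any difference between arms at that visit is chance. Comparing baseline means therefore says nothing about DaPI. The baseline score is useful as a covariate, because it explains part of the variation in the later scores.

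The success rule concerns differential improvement, which is either a baseline-adjusted difference between arms or a group-by-time contrast. The stated comparison is of means at each visit. Several tests fit the sentence, and they differ in power and in what they estimate. Leaving the choice open also leaves room to pick a test after seeing the data.

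A paired t-test compares parents with themselves. It makes no use of the waitlist arm, which is there to separate the programme from retest effects, regression to the mean and the child's growing older. The abstract gives it no stated role.

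**Working it through.** **Inputs from the protocol.** Effect size d = 0.50, alpha 0.05, power 0.80, minimum N = 128, 1:1 allocation, three visits.

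**Assumptions.** The protocol gives no correlation between visits. I take r = 0.3 to 0.8, equal for each pair of visits, SD = 1, arm difference 0 at baseline and 0.5 at both follow-ups, and a single outcome. Tests are two-sided at 0.05.

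**The plan's own figure.** An exact two-sided two-sample t-test at d = 0.5 needs 63.77 per arm, rounded up to 64, so 128 in total, with power 80.1%. A one-sided test would need 100 in total and does not match. The stated 128 therefore corresponds to an unadjusted comparison of two arms at one visit.

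**Readings of the analysis sentence, n = 64 per arm**

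1. Group effect averaged over all three visits. The mean difference is (0 + 0.5 + 0.5)/3 = 0.333 and the variance of the average is (1 + 2r)/3. At r = 0.6 the standardised effect is 0.333/sqrt(0.733) = 0.389.
2. Multivariate group-by-time test (the two changes from baseline). Noncentrality is (n/2) × 2d²/[3(1 − r)]. At r = 0.6 this is 32 × 0.5/1.2 = 13.33, with 2 numerator df.
3. Multivariate test of all three scores. Noncentrality is (n/2) × 2d²/[(1 − r)(1 + 2r)]. At r = 0.6 this is 32 × 0.5/0.88 = 18.18, with 3 numerator df.

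**Baseline-adjusted alternatives**

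4. Multivariate test of post and 1-month scores given baseline. The noncentrality is the same as in 3, but with 2 numerator df.
5. ANCOVA of the post score. The standardised effect is d/sqrt(1 − r²). At r = 0.6 it is 0.5/0.8 = 0.625.

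| Test | r = 0.3 | 0.5 | 0.6 | 0.7 | 0.8 |
|---|---|---|---|---|---|
| 1. Average of three visits | 73% | 63% | 59% | 55% | 52% |
| 2. Multivariate group-by-time | 68% | 83% | 91% | 97% | 99.7% |
| 3. Multivariate, all three scores | 89% | 93% | 95.5% | 98% | 99.8% |
| 4. Multivariate, baseline-adjusted | 93% | 95% | 97.3% | 99% | 99.9% |
| 5. ANCOVA, post score | 84% | 90% | 94% | 98% | 99.7% |

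Tests 3 and 4 share a noncentrality because a multivariate test uses the correlation between visits. A baseline component with no expected difference still carries most of the covariate information. The cost of treating it as an outcome is one extra numerator degree of freedom, at most about 4 percentage points. Against test 4, the group-by-time test loses about 24 points at r = 0.3 (68% against 93%; 68.4% against 92.7% before rounding) and almost nothing at r = 0.8. The averaged effect loses most, and its loss grows with r.

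**Paired t-test with no programme effect.** Suppose both arms drift by m SD for reasons unrelated to DaPI (assumed). The within-arm standardised change is m/sqrt(2(1 − r)). For m = 0.2 and r = 0.6 it is 0.2/sqrt(0.8) = 0.224. With 64 per arm and r = 0.6, an arm reaches p < 0.05 in 14%, 42% and 75% of trials for m = 0.1, 0.2 and 0.3. Over r = 0.5 to 0.7 the range is 12% to 86%. If that probability is p, DaPI is significant and the waitlist arm is not with probability p(1 − p), which is 11% to 25% over the same range.

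**The case against.** The strongest reply is that the sentence is shorthand. Measurements before and after in two groups, with a success rule about differential improvement, plausibly imply a repeated-measures model with a group-by-time term. That term would be a valid, unbiased test of the rule, and preferring baseline adjustment to it is a matter of efficiency. The method named is also an analysis of covariance, so some covariate is presumably intended, and a condensed article may leave covariates to an analysis plan that is not shown. All of this stands. It limits the point to what the text fixes: baseline is listed among the compared means, and the contrast that decides success is not identified.

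Three stronger readings are tempting, and the documents do not support them.

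- A reader might infer that the planned analysis has about 59% power where 94% was available. The 59% belongs to an effect averaged over three visits at r = 0.6, and the protocol does not name that test. The multivariate test of all three scores has 95.5% at the same r.
- A reader might infer that the protocol rules baseline out as a covariate, or that no MANCOVA could test improvement. The text says neither.
- A reader might infer that the paired t-test could declare DaPI effective. The success rule is explicitly a comparison with control, so a within-arm p-value cannot meet it. The risk is a misleading secondary claim, and its size rests entirely on the assumed drift.

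**Conclusion.** The point holds as a mismatch within the document. The stated comparison includes a score that cannot reflect the intervention, and it does not identify the contrast that the success rule needs. The abstract and the analysis section also disagree about the paired t-test.

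No single figure gives the size. With 64 per arm, d = 0.5 at both follow-ups and equal correlations, the loss against a baseline-adjusted multivariate test is at most about 4 points if all three scores are tested jointly. It ranges from about 24 points to almost nothing for a group-by-time test, as r rises from 0.3 to 0.8. It is about 20 to 48 points if the group effect is averaged over visits (93% against 73%, and 99.9% against 52%). The correlation is an assumption throughout. For the paired t-test the harm is a possible false impression of benefit, not lost power.

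**What to change.** - Analyse the post-intervention and 1-month scores as outcomes, with that outcome's baseline value as covariate. Either ANCOVA or a longitudinal mixed model with arm, visit and arm-by-visit would serve.
- State that the baseline-adjusted between-arm contrast from this model decides success, and at which visit or visits it is read.
- Delete the paired t-test from the abstract, or label it descriptive there and in the Statistical analyses section, so that the two agree.

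The cost is a few lines of wording in the protocol and analysis plan. Baseline is already collected, so there are no new data, visits or participants. The change should be made before any analysis by arm.

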### Objective

The overarching aim of this study is to determine whether a universal, digital-assisted preventive parenting intervention named DaPI will be effective in promoting the mental health of children by targeting parenting behavior and parental self-efficacy. We hypothesized that parents in the DaPI program would report lower rates of ineffective parenting behavior and higher parenting self-efficacy (primary outcomes), which would lead to improved mental health in their child (secondary outcomes, i.e., better behavior and emotional adjustment).

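### Success rule: any one outcome variable, primary or secondary, at an unadjusted 0.05 and at no named time point is enough to declare DaPI effective

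*Protocol article*

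**What the plan says.** The decision rule is in the last sentence of Statistical analyses. DaPI succeeds if its parents "show more improvement over time on one of the outcome variables compared to the control group, at a significance level of 0.05". The same sentence adds a second condition: the standardised difference d must lie between 0.2 and 0.5. Before that, the section plans a MANCOVA to "compare the mean of the outcome variables at pre-assessment, post-assessment, and 1-month follow-up between the two groups", and then: "Pairwise comparisons will be performed to identify specific differences in the outcome variables between the groups".

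The outcome variables are defined elsewhere in the protocol:

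- **Primary outcomes.** These are parenting behaviour (MAPS) and parental self-efficacy (CAPES efficacy subscale). On MAPS: "This 34-item scale comprises two broad domains (i.e., Positive and Negative Parenting) and seven narrowband domains of parenting practices". Score interpretation is given for the two broad domains.
- **Secondary outcome.** This is child mental health on the 30-item CAPES child scale. It has two subscales (behavioural problems, emotional maladjustment) and a total score of 0-90.
- **Timing.** Questionnaires are completed "at pre- (baseline) and post-intervention (8 weeks) and at the 1-month follow-up mark". Neither post-baseline time is called decisive.

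Sample size and power analysis plans for d = 0.50, alpha 0.05 and power 0.80, with a minimum of 128 and a target of 200.

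**The concern.** A rule satisfied by any one of several tests, each at 0.05, does not have a 0.05 error rate for the conclusion it produces. Four features combine here: several outcome scores, two post-baseline times, no adjustment or hierarchy, and no limit to the primary outcomes. Because of the last, a chance result on a child subscale, with nothing on parenting or self-efficacy, would satisfy the rule.

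This is a stated criterion for the trial's headline conclusion, so it cannot be treated as detail left to an analysis plan. A plan that controlled the error would have to override it. The Discussion ties a finding of effectiveness to wide dissemination among Malaysian parents and to investment by policymakers, so a false claim would matter.

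**Working it through.** **1. The plan's own figure.** A two-sided two-sample t-test at alpha 0.05, d = 0.50 and power 0.80 needs 63.77 per arm, rounded to 64, or 128 in total. The stated minimum is reproduced. A one-sided test needs about 51 per arm (102) and does not fit. The sample size therefore rests on one two-sided comparison, whereas the success rule allows several.

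**2. Which event to count.** The rule needs more improvement under DaPI, so only results in DaPI's favour can trigger it. For one two-sided test at 0.05 that chance is 0.05 / 2 = 2.5%.

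**3. How many tests.** The count depends on the reading:

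- 3 outcomes: for example MAPS negative, self-efficacy and the CAPES child total; or the two MAPS broad scores and self-efficacy.
- 5 outcomes: MAPS positive, MAPS negative, self-efficacy, child behavioural problems, child emotional maladjustment.
- One test per outcome if improvement over time means a single group-by-time test; two if each post-baseline time counts.

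**4. Chance of a false claim when DaPI has no effect on anything.** For k independent tests the chance of at least one favourable result is 1 - (1 - 0.025)^k:

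- k = 3: 1 - 0.975^3 = 7.3%
- k = 5: 1 - 0.975^5 = 11.9%

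Correlation lowers this. The protocol gives no correlations, so I assumed 0 to 0.7 between outcomes and 0.7 between the two times, and simulated 400,000 multivariate normal draws per setting.

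| Tests | In DaPI's favour | Any p < 0.05, either direction |
|---|---|---|
| 3 outcomes, one test each | 5.4-7.3% | 10.9-14.3% |
| 5 outcomes, one test each | 7.4-11.9% | 14.8-22.6% |
| 3 outcomes, two times | 8.9-12.0% | 17.7-22.9% |
| 5 outcomes, two times | 11.8-19.2% | 23.4-35.4% |

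The lower end of each range is at outcome correlation 0.7, the upper end at 0.

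**5. The effect-size condition.** The smallest d that reaches p < 0.05 is t(0.975; 2n - 2) × sqrt(2/n):

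- 50 per arm: 0.40
- 64 per arm: 0.35
- 100 per arm: 0.28

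All exceed 0.2, so any significant result already meets the lower bound. With baseline adjustment at an assumed correlation r = 0.6, these shrink by sqrt(1 - 0.36) = 0.8 to 0.32, 0.28 and 0.22, still above 0.2. The upper bound, read literally, disqualifies an effect above 0.5. It lowers the error only slightly: for 5 outcomes at two times, 50 per arm and outcome correlation 0.3-0.5, from about 14-17% to about 13-14%.

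**6. The MANCOVA as a gate.** If a significant omnibus test were required first, the chance of any claim under the global null would be at most 5%, and about 1.6-3.0% in DaPI's favour for 5 outcomes. The protocol does not state that requirement.

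**The case against.** The strongest defence is the order of the analysis. The omnibus MANCOVA comes first and the pairwise comparisons can be read as follow-up to it; with such a gate the global-null error would be controlled. But neither the pairwise comparisons nor the success rule is made conditional on the omnibus result. Even a stated gate would leave the remaining outcomes unprotected once one has a true effect. If self-efficacy alone moved, the gate would tend to open and the child scores would again be tested at an unadjusted 0.05. This part of the defence shows an ambiguity and does not remove the fault.

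A second defence is that improvement over time means one test per outcome and that only primary outcomes were intended. The first half is a fair reading and is covered by the one-test rows. The second is not what the text says. On both together, 3 primary scores give 5-7% in DaPI's favour, which is 2 to 3 times the nominal 2.5% but only slightly above 5%. The size of the problem does depend on the reading.

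Three stronger conclusions are tempting and are not supported:

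- **That the false-claim rate is 23% or 40%** (1 - 0.95^5 and 1 - 0.95^10). Those figures assume independence and count results favouring the control group, which cannot trigger the rule.
- **That the seven MAPS narrowband scores add to the count.** They are described, but nothing places them in the success rule.
- **That success on a parenting score alone disregards the primary/secondary split.** Parenting behaviour is a primary outcome, so such a result respects the split. The fault is the reverse: a secondary score alone is enough.

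**Conclusion.** The concern holds. As written, the rule allows a claim of effectiveness at well above the nominal 2.5% in DaPI's favour: roughly 2 to 5 times with one test per outcome (5-12%) and 4 to 8 times with two times (9-19%). The exact multiple rests on the assumed correlations and on whether 3 or 5 outcomes count. On every one of these readings the error exceeds nominal. Measured against the full 0.05, the excess runs from slight (5.4%) to nearly fourfold (19.2 / 5 = 3.8). The rule should be corrected before any outcome data are analysed by group, because it governs the trial's main conclusion.

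**What to change.** Replace the last sentence of Statistical analyses with a rule containing these elements:

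- **Confirmatory family.** Parental self-efficacy and the MAPS score or scores named in advance, at one time point named in advance, tested with Holm at overall two-sided alpha 0.05. Which MAPS score or scores and which time point is the sponsor's choice.
- **Scope of the claim.** Effectiveness is claimed only for the construct that succeeds.
- **Child mental health.** A claim only through a named CAPES child score, tested after primary success with the overall error controlled. With ordinary Holm, the full alpha passes on only if every primary succeeds; if one success is to open the gate, a truncated Holm or graphical procedure is needed.
- **Everything else.** Other scores and the other time point are reported as estimates with confidence intervals and cannot trigger the claim.
- **Effect size.** Report d with its interval. Drop the upper bound of 0.5 as a success condition; the lower bound adds nothing.
- **MANCOVA.** If kept, state its role.

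The change is one of wording; the cost is power. With two primaries and d = 0.5, the first Holm step uses alpha 0.025. Without baseline adjustment:

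| Per arm | alpha 0.05 | alpha 0.025 |
|---|---|---|
| 50 | 70% | 59% |
| 64 | 80% | 71% |
| 100 | 94% | 90% |

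With three primaries (alpha 0.0167) power is 53%, 66% and 87%. Adjusting for the baseline score recovers much of the loss: at an assumed r = 0.6 the effective d is 0.5 / 0.8 = 0.625, and power at alpha 0.025 is 80% at 50 per arm and 90% at 64.
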